### Statistical analysis

Quantitative data analysis will be conducted using R [77]. Descriptive statistics will be reported for the samples of patients and GPs (e.g., socio-demographics, treatment fidelity, characteristics of recruited PC practices). Scores for feasibility and acceptability items will be presented graphically for the IG and CG treatment groups, along with patients’ trajectories in both transdiagnostic and disorder-specific outcomes. The potential effectiveness of both treatment conditions will additionally be estimated via linear mixed models with restricted maximum likelihood estimation (REML), known to perform well with small sample sizes [78]. Changes over time in patients’ beliefs about emotions (EBQ), emotion suppression /cognitive reappraisal (ERQ), experiential avoidance (EBAQ) and negative affectivity (PID-5-BF + M) will be examined. Treatment group (IG, CG), time (t0, t1) and their interaction will be included as fixed effects. To account for the assumed ICC of recruited PC practices, patients’ practice affiliation will be modelled as a random effect, with the interaction between practice and time specified as a random slope. Changes over time in patients’ symptoms of depression (PHQ-9), anxiety (GAD-7) and somatoform disorder (PHQ-15) will also be analysed using linear mixed models.

To avoid missing values for digitally collected data, all questions in SoSci Survey [56] must be answered before completing data entry. Missing values for partially completed (printed) questionnaires will be imputed if deemed necessary. As the pilot study will not be adequately powered to assess treatment effectiveness, for all statistical tests, only the confidence interval limits will be reported without relying on the *p*-value [42, 79].

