## Methods

### Design

The pilot study will adopt a parallel-group, two-arm, cluster randomised controlled design. It adheres to the CONSORT statement extension to randomised pilot and feasibility trials [42] and to the SPIRIT guidelines [43] (Additional file 1). Using a 1:1 allocation ratio on PC practice level, GPs will provide patients with either a transdiagnostic intervention (i.e., intervention group (IG)) adapted from the UP [24], or with iTAU (i.e., control group (CG)) based on official German guidelines for the treatment of a depression, anxiety or somatoform disorder [44–46]. In both study groups, treatment will consist of four 20-min sessions administered over 12 weeks. Data collection will take place at baseline (patients only) and after treatment completion (patients and GPs) (Fig. 1).

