#### Randomisation

Once at least one GP of a PC practice agrees to participate, cluster randomisation will be conducted at practice level as per a computer-generated sequence in a 1:1 ratio. This approach was chosen to prevent spillover effects within clusters, such as when several GPs from one practice participate in the study [49]. To ensure an even distribution of patients between IG and CG, randomisation will be stratified by the number of GPs in a practice providing treatment, assuming that practices with more participating GPs will treat more patients. As part of the consecutive recruitment, for each practice stratum (e.g., two participating GPs per practice), the first practice recruited is randomly allocated to either the IG or CG using the RANDBETWEEN function in Microsoft Excel [50]. This function generates an integer within a specified range (e.g., 1 or 2), with each value having an equal probability of being selected, thereby ensuring fairness in allocation. Within one stratum, the next recruited practice will be assigned to the opposite study group, and so forth. If a study group is underrepresented when a stratum is newly formed (i.e., more practices have been assigned to either study group overall), this study group will be prioritised for allocation to prevent imbalance in the distribution of practices.

Randomisation will be managed and documented by a staff member of the Institute of General Practice at LMU Munich, who is not part of the study [50]. Allocation concealment will be maintained using opaque envelopes, which will be opened by study staff only shortly before GPs are trained in their assigned treatment condition.

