#### Sample size

No formal sample size calculation is required for a pilot study [51]. To minimise the maximum likely error for any calculated rates to less than 10%, Eldridge et al. [52] suggested a total of 23 clusters for cluster-randomised pilot studies with a cluster size of five participants, assuming an intra-cluster correlation (ICC) of 0.05. Similar ICCs were found for psychological outcomes in German PC [53] and recruiting six patients per PC practice was considered feasible for psychological interventions [54, 55]. To balance scientific considerations and practical constraints (i.e., time and staff resources), a sample size of 100 patients across 20 PC practices is anticipated, with six patients enrolled per practice, accounting for an expected 20% dropout rate. This should provide sufficient data to adequately assess treatment feasibility, acceptability and potential effectiveness, forming a robust basis for a confirmatory main trial.

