#### Secondary outcome measures

At t_0_ and at t_1_, patients will complete self-report diagnosis-specific and transdiagnostic questionnaires. Potential effectiveness will be based on change in transdiagnostic factors relevant to emotion-based disorders [27, 28], thus serving as surrogate outcomes [42] for patients’ improvement in mental health.

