Brief Experiential Avoidance Questionnaire (BEAQ): The BEAQ [68] comprises 15 items rated on a 6-point Likert scale (1: “strongly disagree” to 6: “strongly agree”). It matches the content of the third session of the transdiagnostic intervention as it measures a tendency towards emotion-based avoidance. A higher overall score, varying between 15 and 90, suggests a greater extent of experiential avoidance. With the German BEAQ, five dimensions of experiential avoidance can be monitored: behavioural avoidance, distress aversion, procrastination, distraction/suppression and repression/denial. In a mixed sample of students and outpatients, the BEAQ yielded satisfactory internal consistency (α = 0.80) and test–retest reliability (r = 0.77). Discriminant and convergent validity were also shown [69].

Modified Personality Inventory for DSM-5 Brief Form (PID-5-BF + M): The PID-5-BF + M [70] assesses the personality traits of psychoticism, disinhibition, detachment, antagonism, anankastia and negative affectivity. Only the latter subscale will be employed in the pilot study, as negative affectivity (i.e., neuroticism) is the core transdiagnostic concept upon which the UP was developed [71]. Negative affectivity is measured with six items on a 4-point Likert scale (0: “very false or often false” to 3: “very true or often true”). Ranging between 0 and 18, a higher subscale score suggests greater negative affectivity. Norm values for the PID-5-BF + M were established for the German population [72]. In a PC sample, satisfactory reliability scores (α = 0.68—0.81) as well as convergent and discriminant validity were observed [73].

Kessler Psychological Distress Scale-6 (K-6): The K-6 [47] comprises 6 items that examine psychological distress over the last 30 days. Responses are given on a 5-point Likert scale (0: “none of the time” to 4: “all of the time”). The total score can range from 0 (no psychological distress) to 24, with higher values suggesting more distress. Commonly used in the PC setting [74], the K-6 will only be administered at t_0_ to complement GPs’ judgment of a patient’s psychological distress level. Established age-specific norm values for the German population will be provided to GPs [48]. The German Kessler-10, a longer version of the K-6 with four additional items, was found to have high internal consistency (students: α = 0.80; outpatients: α = 0.90) as well as satisfactory convergent validity [75].

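### The listed mixed model estimates a difference in change and does not condition on the baseline score, so its confidence limits are wider than they need to be

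*Protocol article*

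**What the plan says.** The Statistical analysis section of the protocol article fixes the model for the transdiagnostic scales: "Treatment group (IG, CG), time (t0, t1) and their interaction will be included as fixed effects". On clustering it adds that "patients’ practice affiliation will be modelled as a random effect, with the interaction between practice and time specified as a random slope". The depression, anxiety and somatic symptom scores are also to be analysed with linear mixed models. Estimation is by restricted maximum likelihood (REML), and only confidence limits will be reported.

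Baseline values exist for every scale concerned. Under Secondary outcome measures, at both t0 and t1, "patients will complete self-report diagnosis-specific and transdiagnostic questionnaires".

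Under Randomisation, "randomisation will be stratified by the number of GPs in a practice providing treatment". The reason given is to even out patient numbers between the arms. This factor is not among the listed fixed effects.

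The Sample size section says "a sample size of 100 patients across 20 PC practices is anticipated, with six patients enrolled per practice, accounting for an expected 20% dropout rate". The Design section says "Using a 1:1 allocation ratio on PC practice level", which means about 10 practices per arm. No t0–t1 correlation is given for planning. The only test–retest value for a modelled scale is 0.77 for the experiential avoidance questionnaire (BEAQ), from a mixed sample of students and outpatients.

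**The concern.** With a free group effect at t0, each arm keeps its own baseline mean, and the group-by-time coefficient is the difference between arms in mean change. The t0 score enters as an outcome and is never conditioned on. Adding a patient random effect does not alter this.

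With few practices per arm, some baseline imbalance by chance is likely. A change-score contrast subtracts all of it, although only a fraction r is expected to persist to t1. The result is extra variance. In a given trial with a visible imbalance, the estimate is also shifted.

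At stake is the width of the confidence intervals. They are the whole of the reported inference on potential effectiveness, and potential effectiveness is one of the elements in the decision to proceed to a main trial.

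**Working it through.** **The plan's own figure.** The only figure in the article that follows from a formula concerns rates: "suggested a total of 23 clusters for cluster-randomised pilot studies with a cluster size of five participants, assuming an intra-cluster correlation (ICC) of 0.05". With design effect 1 + (5−1) × 0.05 = 1.20, the number of patients for a 10% half-width is 1.96² × 0.25 × 1.20 / 0.10² = 115.2. Divided by 5 this is 23.05 clusters, so the 23 reproduces. No precision is stated for the mixed-model effect, so nothing further can be reproduced.

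**Inputs.**
- From the Sample size section: 20 practices × 6 enrolled = 120, or 60 per arm. After 20% dropout 96 remain, or 48 per arm and 4.8 per practice. ICC 0.05.
- Assumed: the t0–t1 correlation r, shown from 0.3 to 0.9; equal variances at t0 and t1.

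**Variance per patient, in units of σ².**
- Difference in change: 2(1−r).
- Conditioning on t0: 1−r².
- Ratio: 2(1−r)/(1−r²) = 2/(1+r).

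This is the complete-case comparison. A REML model with a patient effect also uses the t0 scores of patients who drop out. The ratio then becomes 1 + [(1−r)/(1+r)] × (48/60).

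| r (assumed) | 2(1−r) | 1−r² | 2/(1+r) | Interval wider by | Ratio with dropouts' t0 scores |
|---|---|---|---|---|---|
| 0.3 | 1.40 | 0.91 | 1.54 | 24% | 1.43 |
| 0.5 | 1.00 | 0.75 | 1.33 | 15.5% | 1.27 |
| 0.6 | 0.80 | 0.64 | 1.25 | 12% | 1.20 |
| 0.7 | 0.60 | 0.51 | 1.18 | 8.5% | 1.14 |
| 0.77 | 0.46 | 0.41 | 1.13 | 6% | 1.10 |
| 0.9 | 0.20 | 0.19 | 1.05 | 3% | 1.04 |

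The fifth column is √(2/(1+r)) − 1. These are large-sample formulas and ignore the small loss from estimating the baseline slope.

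**Clustering.** With clusters, the relevant r is that of practice means. At ICC 0.05 and five per practice, a practice-level correlation assumed between 0.5 and 1.0 gives a complete-case cost of 25–33% at patient-level r = 0.5, 14–21% at 0.7 and 10–17% at 0.77.

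**Interval width.** Design effect 1 + 3.8 × 0.05 = 1.19, applied to both analyses. The standard error is √(2 × 1.19/48 × variance factor), multiplied by t(18 df) = 2.10.
- r = 0.5: half-width 0.47 against 0.41 SD.
- r = 0.6: 0.42 against 0.37 SD.
- r = 0.7: 0.36 against 0.33 SD.
- r = 0.77: 0.32 against 0.30 SD.

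**Size of chance imbalance.** The baseline difference between arms has standard error √(2 × 1.19/48) = 0.22 SD. It exceeds 0.2 SD in either direction in about 37% of trials (normal approximation). Given an imbalance d, the change-score estimate is shifted by (1−r)d in the opposite direction. For d = 0.2 SD and r = 0.5 that is 0.1 SD.

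**Stratification factor.** It enters none of these formulas. In balanced data, a practice-level main effect that is constant over time leaves the group-by-time estimate unchanged.

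**The case against.** **The correlation is unknown.** This stands. A reader might infer a fixed loss of 18–33%, but that range is only r = 0.5 to 0.7. At 0.77 the complete-case cost is 13%. That value comes from another sample, so it does not settle r for these patients either. The cost must be read as a function of r.

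**REML already recovers part of the loss.** This stands if a patient-level effect is fitted. The dropouts' t0 scores bring the cost down to about 27%, 20%, 14% and 10% at r = 0.5, 0.6, 0.7 and 0.77.

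**The model suits the stated aim.** The article sets out to follow trajectories and change over time, and group-by-time is a valid model for that. It is not an unadjusted analysis, since baseline is subtracted. That supports keeping it for description, but not as the most precise estimate of the difference between arms.

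**Imbalance may not be due to chance.** Unblinded GPs choose patients from their own pool, apparently after their practice has been allocated. If recruitment differs between arms, neither the change-score nor the baseline-conditioned estimate is guaranteed to be unbiased. This limits the argument to precision under chance imbalance, and is a reason to show both analyses.

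**Stronger readings.** A reader might infer that the group-by-time estimate is biased by regression to the mean. Over repeated randomisations the difference in change is unbiased. The shift shown in the working is conditional on the imbalance observed. A reader might also infer that omitting the stratification factor adds to the loss. Its stated purpose is to balance patient numbers, and no association with outcome is documented.

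**No patient-level random effect is listed.** Fitted literally, the model treats a patient's two scores as independent given practice. In a small simulation (20 practices of five, ICC 0.05, 30 runs per setting) the reported standard error was about 0.30 against an empirical 0.19 at r = 0.5, and 0.31 against 0.15 at r = 0.7. The intervals would then be much too wide. An article may leave the patient effect to the full plan, so this is a caveat on the figures and not a separate finding.

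**Conclusion.** The point holds as a minor one. The listed model estimates a difference in mean change and does not condition on a baseline score that the trial collects. Conditioning is more precise at any r below 1, provided the arms share the same expected baseline. For patients with both scores the cost is 2/(1+r), which runs from 54% at r = 0.3 to 5% at r = 0.9. It is smaller when a patient effect brings in the dropouts' t0 scores. In interval half-width the gain is about 0.02 to 0.06 SD for r between 0.77 and 0.5. All these figures rest on assumed values of r.

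Severity is low. Effectiveness is a secondary aim of a pilot with no power claim and no progression threshold, and a gain of this size would overturn no stated decision. The documents support neither a claim of bias over randomisations nor any precision loss from leaving out the stratification factor.

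**What to change.** In the Statistical analysis section, state that for each scale the effect is the IG–CG difference at t1. Estimate it from a REML model with group and the patient's t0 score as fixed effects and practice as random intercept. An equivalent route is to keep the longitudinal model, include a patient effect, and constrain the arms to a common mean at t0.

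Keep the group-by-time model, with a patient effect, for describing trajectories and as a sensitivity analysis.

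Adding the number of participating GPs as a covariate is optional. It would reflect the randomisation design at a cost of about one practice-level degree of freedom, and it should not be justified by the precision figures above.

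The cost is analysis wording only: no new data, visits or patients.

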### Data collection and management

Patient recruitment started on June 1^st^ 2024 and is scheduled until March 31^st^ 2025, with data collection to be completed by June 30^th^ 2025. Participants will be enrolled by GPs consecutively, at the latest 12 weeks prior to the end of the data collection period. Data of patients (t_0_ and t_1_) and GPs (t_2_) will be collected using the online platform SoSci Survey [56] and stored on a secure internal server of the Institute of General Practice at LMU Munich. Data collected by printed questionnaires will be securely stored at the study site, with access restricted to study staff. The sociodemographic, health and treatment assessment related data will be collected in pseudonymised form. Patients create their own pseudonym based on predefined criteria (e.g., the first letter of their mother’s and father’s name) which has to be entered t_0_ at and t_1_. GPs are assigned one numerical code per practice to be used at t_2_. Personal data (e.g., name, telephone number) which is requested from GPs and patients as part of obtaining informed consent will be stored separately from their sociodemographic, health and treatment related data. Two lists are kept at the Institute of General Practice at LMU Munich documenting the names of patients/GPs and their pseudonyms. Both lists are protected by technical and organisational means against unauthorised third-party access. Decoding will only take place in the event that contacting patients for data collection outside of their PC practice becomes necessary, patients’ safety requires it (i.e., medical reasons) or the scientific question changes (i.e., scientific reasons). For decoding data due to scientific reasons, the approval of the ethics committee at LMU Munich is obtained beforehand.

No data monitoring committee will be installed due to the unblinded, non-invasive, short-term character of the pilot study. Further, GPs and patients can request the deletion of their stored data at any time. Person-identifying data will be deleted after the end of the research project, or as soon as the study objective has been reached. The remaining anonymised data will be stored for at least 10 years and deleted at the latest 15 years after their acquisition unless legal requirements stipulate longer archiving obligations.

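### If fitted as written, the mixed model has practice effects but no patient effect, so the group-by-time confidence intervals are too wide

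*Protocol article*

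**What the plan says.** In the protocol article, Statistical analysis, potential effectiveness is estimated with linear mixed models fitted by REML. The fixed part is listed: "Treatment group (IG, CG), time (t0, t1) and their interaction will be included as fixed effects". The random part comes next. Its only stated purpose is to handle clustering: "To account for the assumed ICC of recruited PC practices". The terms themselves are then set out in these words: "practice affiliation will be modelled as a random effect, with the interaction between practice and time specified as a random slope". Neither that section nor any other names a patient random effect, nesting of patients in practices, or a residual correlation between a patient's two scores.

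The data are paired. Under Secondary outcome measures: "At t_0_ and at t_1_, patients will complete self-report diagnosis-specific and transdiagnostic questionnaires". Under Data collection and management, patients enter a self-made pseudonym at both time points, so the pairs can be linked.

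On reporting, Statistical analysis says that for all tests "only the confidence interval limits will be reported without relying on the" p-value. The symptom scales PHQ-9, GAD-7 and PHQ-15 are also to be analysed with linear mixed models, whose terms are not restated.

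**The concern.** The effect of interest is the group-by-time interaction, which compares the change within patients between arms. Its precision depends on how strongly a patient's t0 and t1 scores correlate. Under the written random structure, two scores from one patient are no more alike than scores from two different patients of the same practice at the same two times. All stable between-patient variance then falls into the residual, and the variance of a change score is overstated.

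At stake are the intervals for the five transdiagnostic scores (EBQ, ERQ suppression, ERQ reappraisal, BEAQ, negative affectivity), and for the three symptom scales if the same model is used. With no p-values reported, these limits carry the whole inferential message on potential effectiveness. Limits labelled 95% would behave like limits of a higher level and hide precision that the trial has.

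**Working it through.** **The plan's own figure.** The protocol states no interval width for the mixed models. Its one precision figure (Sample size) is 23 clusters of five for an error below 10% in a rate, at ICC 0.05. It reproduces: 1.96 × √(0.25 × (1 + 4 × 0.05) / (23 × 5)) = 10.0%. It concerns rates and does not bear on this model.

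**Inputs from the protocol.** "a sample size of 100 patients across 20 PC practices is anticipated, with six patients enrolled per practice"; 1:1 allocation by practice; ICC 0.05; two measurements per patient. I take 10 practices per arm and m = 100/20 = 5 patients with complete pairs per practice.

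**Assumed inputs.** Total variance 1. Within-patient t0–t1 correlation ρ from 0.3 to 0.77. The upper end is borrowed from the BEAQ test–retest value (Transdiagnostic outcomes), which comes from another sample and is not a correlation across 12 weeks of treatment. Practice-by-time slope variance τ²: 0 or 0.05.

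**Step 1, correct variance.** With practice variance 0.05, patient variance ρ − 0.05 and error variance 1 − ρ, the interaction has variance (2/10) × [τ² + 2(1 − ρ)/5]. At τ² = 0 and ρ = 0.5: 0.2 × 0.2 = 0.04, so SE = 0.200 SD.

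**Step 2, variance under the written model.** Patient variance joins the residual, which becomes 0.95. With the fitted slope variance at zero: (2/10) × 2 × 0.95/5 = 0.076, so SE = 0.276 SD whatever ρ is. At ρ = 0.5 this is 0.276/0.200 = 1.38 times the true SE.

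**Step 3, what the slope can absorb.** To match the real spread of practice-mean changes, the fitted slope variance would have to be about τ² − 2 × (patient variance)/m. It cannot go below zero, so it stays at zero while τ² is below about 2(ρ − 0.05)/5:
- ρ = 0.3: 0.10
- ρ = 0.5: 0.18
- ρ = 0.7: 0.26

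Below that limit the written SE stays near 0.276 while the true SE rises with τ², so the excess shrinks. At or above it the slope absorbs the excess.

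**Step 4, REML simulation** (20 practices × 5 patients × 2 times, 300 runs per setting). Ratio of the SE under the written model to the SE with a patient intercept added:

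| ρ | τ² = 0 | τ² = 0.05 |
|---|---|---|
| 0.3 | 1.11 | 1.09 |
| 0.4 | 1.19 | 1.15 |
| 0.5 | 1.30 | 1.25 |
| 0.6 | 1.42 | 1.36 |
| 0.7 | 1.62 | 1.49 |
| 0.77 | 1.83 | 1.69 |

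At ρ = 0.5 and τ² = 0 the mean SEs were 0.272 and 0.211, giving half-widths of 1.96 × 0.272 = 0.53 SD and 1.96 × 0.211 = 0.41 SD. Coverage of nominal 95% intervals was 97 to 100% under the written model and about 94 to 98% with the patient intercept. In a further simulation with τ² = 0.1 the ratios fell to about 1.05 to 1.3.

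**Step 5, cross-checks.** With six enrolled per practice and 20% missing t1 (40 runs per setting; comparator with practice and patient intercepts but no slope), the ratios were 1.26, 1.33, 1.48 and 1.89 at ρ = 0.4, 0.5, 0.6 and 0.77. The crude factor 1/√(1 − ρ) gives 1.20 at ρ = 0.3 and 2.09 at 0.77. It overstates the ratio because it ignores the variance taken out by the practice intercept and the slope that the correct model also estimates.

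**The case against.** The strongest reply is that the sentence on random effects has a limited purpose, the practice ICC, and does not say that no other term will be fitted. The article is condensed, the pairs can be linked, and statistical code is to be released, so the fitted model may include a patient term. This stands in part: the conclusion must be conditional on fitting the model as written. It does not remove the point. The article sets out the random part down to the slope, and an analyst following it would fit `(1 + time | practice)`.

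A reader might go further and infer more than the documents support:

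- **A fixed inflation of 1.3 to 1.6.** That range depends on an assumed correlation of about 0.5 to 0.7 and a small slope variance. The protocol gives neither.
- **That the practice slope can never compensate.** It absorbs part or all of the excess if practices differ enough in their change over time.
- **Exaggerated benefit.** The error is conservative. The intervals are too wide, and with complete pairs the estimate does not move.
- **A threat to the trial's main conclusions.** Feasibility and acceptability are primary and do not use this model. Under Outcomes, the decision to proceed has no numeric threshold, so no rule depends on these limits.
- **Wrong variances passed to the main trial.** The article speaks only generally of informing that trial. It does not commit to using these variance components to size it.

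**Conclusion.** The model is wrong as written. It omits the patient level for data measured twice per patient, so the group-by-time intervals are too wide and over-cover (about 97 to 100% at a nominal 95%). For an assumed within-patient correlation of 0.3 to 0.77 and a small practice slope variance, the inflation is roughly 1.1 to 1.8 times, and about 1.2 to 1.6 times at 0.5 to 0.7. Over this range and with a small slope variance the direction is always too wide; the size depends on two quantities that the protocol does not state.

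The defect reaches the five transdiagnostic scores, and PHQ-9, GAD-7 and PHQ-15 if they share the model. It is a should-fix rather than a critical flaw, because it is conservative and confined to secondary analyses of a pilot. It still merits correction, since the limits are the only inferential result reported for those outcomes.

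**What to change.** Add a random intercept for patient nested in practice to every mixed model, including the three symptom scales, and say so in the analysis text. In R: `score ~ group*time + (1 + time | practice) + (1 | patient)`, with patient identifiers unique across practices. Equivalent solutions are a within-patient residual correlation, or a model of the t1 score adjusted for t0 with a practice random effect.

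With 20 practices, Kenward-Roger or Satterthwaite degrees of freedom would be a sensible companion, but their absence is not part of this error.

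The cost is one term in the model formula and one sentence. No extra data are needed, because the pseudonym already links the two questionnaires. The change should be made before the analysis is run.
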